### Data management

Original questionnaires are scanned, classified, recognized, verified by the study team at the University of Jena and transferred with the TeleForm®-software (version 10.8, Electric Paper Informationssysteme GmbH, Lüneburg, Germany) into the data base of the data centre of the University of Ulm. All data communication processes, data storage and encoding are specified in detail in a data protection contract according to the European General Data Protection Regulation. Data preparation and statistical analyses will be performed with SPSS (IBM Corp., Armonk, NY), SAS (SAS Institute Inc., Cary, NC, USA) and MPlus (Muthén & Muthén, Los Angeles, CA) at Ulm University.

### Statistical methods

Comparability in all baseline parameters of the two randomized study groups will be described. For the intention-to-treat (ITT) analysis, missing values for withdrawn subjects or participants with missing data at t_1_ to t_3_ will be imputed by MLMI (Maximum Likelihood Multiple Imputation). For each outcome, ten data sets with imputed values (based on linear regression prediction) will be generated and the results pooled to obtain final estimates.

Inference statistic will be performed according to the variable type with χ^2^-test or Fisher exact tests for categorical variables, Mann–Whitney U tests for ordinal or not normally distributed continuous variables, and t-tests for normally distributed continuous variables. Group differences of the confirmatory endpoints will be tested with ANCOVAs (Analyses of Covariance) considering relevant baseline covariates on a two-sided significance level of 5% taking multiple testing into account. Effects of the intervention on secondary outcomes will be analysed accordingly. Additionally, random coefficient models and latent change analyses will be applied to estimate group effects in longitudinal data structures with repeated measurements. The health economic evaluation will include analyses of intervention costs, cost-effectiveness, and possible cost-benefits.

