**Methods/ design:**

A pragmatic randomised controlled trial with 572 caregivers of older adults (≥ 60 years) receiving benefits of one of the two participating long-term care insurances. Participants are assigned (t_0_) to either the ReDiCare intervention or a control group receiving routine care and counselling. Data are collected at baseline (-t_1_), 3-month (t_1_), 9-month (t_2_) and 15-month (t_3_). The 9-month post-intervention assessment (t_2_) is the primary endpoint to evaluate the results on the primary and secondary outcomes, measured by self-reported questionnaires. Depressive symptoms measured with the CES-D are the primary outcome. The main secondary outcomes are physical complaints, utilization of psychosocial resources, caregiver self-efficacy and burden, positive aspects of caregiving and perceived care quality. A process evaluation, including audio tapes, self-report questionnaires and documentation will be conducted to examine internal and external validity of the intervention. Data on direct and indirect costs are collected for the (health) economic evaluation, using a health care perspective and a societal perspective.

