### Sample size

Sample size calculation is based on analyses of covariance (ANCOVA) to compare post-interventions scores of both groups at t_2_ using -t_1_ scores as independent variables. The sample size for the ANCOVA was calculated in a two-step method as proposed by Borm et al. [63]: (1) Calculation of the sample size n as if a t-test on the follow-up scores was carried out, (2) the number of subjects was then multiplied by a “design factor” [(1 – ρ^2^)*n; ρ = correlation between baseline and follow-up scores] to produce the number of subjects required for the ANCOVA.

The calculation is based on data of previous studies [18, 19, 24] with informal caregivers and the following assumptions: (a) An aimed relevant improvement of the CES-D scores of 3 points compared to the control condition (corresponding effect size Cohen’s d of 0.34); (b) depressive symptoms at t_2_ (control: M = 21.0, SD = 10.1; intervention: M = 18.0, SD = 7.6); (c) a correlation ρ = 0.49 between baseline and follow-up measures (the lowest ρ was used); (d) 1- β = .80 (power); and (e) α = .05 for a two-sided t test, (f) a ratio of n (control) / n (intervention) = 1.00. (1) Using a formula for a two-sample t-test (G*Power Vs. 3.1.9.2) [64] the required total sample size is 282. (2) The required adjusted sample size for ANCOVA with the same power as the t-test is 216 [design factor: (1- 0.49^2^)*n (total)].

Possible different strategies to promote study participation of the two participating insurances are an element of uncertainty in the sample size calculation. Therefore, we added an additional 10% to the calculated 216 participants to compensate a possible shift in variance. Taking this into account, the aimed sample size is 238.

Based on the same assumptions (two-sided t-test, α = .05, 1- β = .80, d = .34) and data of our previous work, the correlations between baseline and follow-up measures of secondary outcomes are expected to be ρ = .40 (VAS Mood), ρ = 0.72 (GBB-24), 0.59 (SPSI-R:S / Subscale “Negative problem orientation”), and ρ = 0.70 (SCQ-AB / Subscale “satisfaction with one’s own performance”). Because of these higher correlations in comparison to the CES-D we assumed that the total sample size of 216 participants will be sufficient to detect at least moderate effects in all secondary outcome measures except the ‘VAS Mood’. For this scale, the aimed sample size of 238 is still sufficient. 

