Based on our previous studies we assumed dropout rates of 15% between -t_1_ and t_1_ and 20% in each of the following two 6-month intervals (t_1_ to t_2_, t_2_ to t_3_). Based on these assumptions we aim to enrol 572 caregivers. The participant flow and numbers through the study are summarized in Fig. 2.

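### Ten MLMI data sets are few for 32% missing at t2, and under ordinary Rubin pooling the 5% test would run at about 6.3%

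*Protocol article*

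**What the plan says.** The Statistical methods section of the protocol article states that, for the intention-to-treat analysis, missing values at t1 to t3 "will be imputed by MLMI (Maximum Likelihood Multiple Imputation". It continues: "For each outcome, ten data sets with imputed values (based on linear regression prediction) will be generated and the results pooled". It names no pooling or variance rule and does not say in words whether residual noise is added. The confirmatory comparison is an ANCOVA, "considering relevant baseline covariates on a two-sided significance level of 5% taking multiple testing into account".

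The abstract fixes the time point: "The 9-month post-intervention assessment (t_2_) is the primary endpoint". The Sample size section supplies the expected losses: "we assumed dropout rates of 15% between -t_1_ and t_1_ and 20% in each of the following two 6-month intervals".

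**The concern.** As its name says, MLMI imputes from maximum-likelihood estimates. Each data set is generated from the same fitted parameters, and only the residual noise differs between data sets. The spread between data sets therefore does not carry the uncertainty of the imputation model itself. Ordinary Rubin's rules assume that it does, so combining the two gives a standard error that is too small, and the error is in the anti-conservative direction. More data sets do not cure it.

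The number of data sets is a separate matter. With about a third of primary outcomes imputed, ten data sets leave the estimate, and so the p-value, visibly dependent on the random seed. In a confirmatory test a result near the threshold could change sides on re-imputation.

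**Working it through.** **Inputs.** From the Sample size section: dropout of 15% and then 20% up to t2; "control: M = 21.0, SD = 10.1; intervention: M = 18.0, SD = 7.6"; "a correlation ρ = 0.49 between baseline and follow-up measures". From Statistical methods: m = 10 and a two-sided 5% level.

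**The plan's own figures.** Pooled SD = √((10.1² + 7.6²)/2) = 8.94, so d = 3/8.94 = 0.336. The exact t-test needs 141 per arm, or 282, as stated. With the design factor 1 − 0.49² = 0.760, this is 108 per arm, or 216, as stated. Adding 10% gives 237.6, or 238, as stated.

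**Missing share at t2.** 1 − 0.85 × 0.80 = 0.32.

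**Variance algebra.** Let g be the fraction of missing information, set equal to the missing share (imputation from baseline and arm only). Scale the variance of the maximum-likelihood estimate to 1. Then:

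- Within-imputation variance: W = 1 − g = 0.68
- Between-imputation variance with fixed ML parameters: B = g(1 − g) = 0.2176
- True variance of the pooled estimate: 1 + B/m = 1.0218
- Ordinary Rubin total: W + (1 + 1/m)B = 0.68 + 1.1 × 0.2176 = 0.9194
- SE ratio: √(0.9194/1.0218) = 0.949
- Actual two-sided level: 2(1 − Φ(1.96 × 0.949)) = 6.3%

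With m = 50 the Rubin total is 0.9020 against a true 1.0044, a ratio of 0.948 and again 6.3%. Raising m alone does not help here.

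**Simulation check** (null effect, missing completely at random, m = 10, 32% missing, 4,000 replicates):

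| Method | N = 504: SE ratio, type I error | N = 572: SE ratio, type I error |
|---|---|---|
| ML imputation, ordinary Rubin pooling | 0.953, 6.4% | 0.960, 6.2% |
| ML imputation, its own variance formula W/(1 − B/W) + B/m | 1.034, 5.3% | 1.041, 4.9% |
| Posterior draws, Rubin's rules | 1.013, 5.1% | 1.014, 4.6% |

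**If t1 scores are used as predictors.** They cannot help the 15% lost before t1. They can help the 0.85 × 0.20 = 17% lost between t1 and t2. With g assumed to fall to 0.20 or 0.25, the same formulas give SE ratios of 0.980 and 0.969, and levels of 5.5% and 5.8%.

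**Monte Carlo noise, m = 10.** For ML imputation it is √(B/m) = √0.02176 = 0.148 of an SE; for posterior draws it is √(g/m) = √0.032 = 0.179. Take a result that would have z = 1.96 with unlimited imputations and hold its SE fixed. Its 95% range under ML imputation is 1.96 ± 1.96 × 0.148, or z from 1.67 to 2.25, which is p from about 0.095 down to 0.025. At g = 0.20 the range is still 0.027 to 0.087.

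**How many data sets.** To hold the coefficient of variation of the SE at 5% (an assumed target), m = 1 + ½(g/0.05)² = 1 + ½ × 6.4² = 21.5, so 22. Ten data sets give 0.32/√18 = 7.5%. With m = 35 the target is met up to g = 0.05 × √68 = 0.41. The noise at g = 0.32 then falls to √(0.2176/35) = 0.079 of an SE for ML imputation, or √(0.32/35) = 0.096 for posterior draws.

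**The case against.** The strongest reply is that a too-small standard error is not a property of MLMI. It arises only when MLMI is combined with ordinary Rubin's rules, and the article names no rule. Pooling formulas, choice of predictors and imputation by arm are details that a journal article may leave to the full plan. This stands. The standard-error part can be put only conditionally, and predictors and arm-wise imputation are not part of the point.

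Three stronger readings are tempting and are not supported:

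- **About 40% missing at t2.** This figure comes only from working back from the 572 to be enrolled, with later losses of 30% per interval (238/(0.85 × 0.70 × 0.70) = 571.4). The stated rates are 20%. The Protocol amendments section also reports dropout below expectation. The mismatch between 572 and the stated rates is a separate matter, and the planned flow in Fig. 2 is not shown.
- **Imputation by fitted values without noise.** The phrase on linear regression prediction could be read this way, and the test would then be badly inflated. But noise-free predictions from one fitted model would make all ten data sets identical, which does not fit a plan to generate ten and pool them.
- **The larger missing share at t3** (1 − 0.85 × 0.80 × 0.80 = 45.6%). It does not bear on the primary test, which is at t2.

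It is also fair to say that the effects are modest. The efficiency lost by stopping at ten is only about 3% (1/(1 + 0.32/10) = 0.969). Ten is thus a matter of precision and reproducibility, not an error in itself. But the article states the method and the number outright, so both can be judged as written.

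**Conclusion.** The point holds in conditional form and is worth acting on because the remedy is nearly free.

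Unconditionally, ten data sets at 32% missing leave seed-dependent noise of about 0.15 of an SE, enough to move a borderline p-value between about 0.025 and 0.095. If ordinary Rubin's rules are applied to ML-based imputations, the SE is also about 5% too small and the 5% test runs at about 6.3%, or 5.5-5.8% if t1 scores bring the missing information down to 20-25%. If a variance formula suited to MLMI is already intended, this second part largely disappears and only the number of data sets remains.

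The figures assume that losses follow the stated rates, that data are missing completely at random, that g equals the missing share unless noted, and that MLMI carries its usual meaning of fixed ML parameters with residual draws. The 20-25% range is an assumption, not a figure from the article.

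**What to change.** Make three changes in the Statistical methods text or the analysis plan, before the data are unblinded.

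1. Raise the number of imputed data sets from ten to at least about 35. About 22 meet the 5% target at 32% missing; 35 leaves a margin, and 50 would do no harm.
2. Choose and name one of two consistent pairs: (a) imputation parameters drawn from their posterior, with residual noise, pooled by Rubin's rules; or (b) MLMI with the variance estimator made for it. Under (b) the simulated SE was 3-4% too large at ten data sets and 32% missing, an error on the safe side.
3. Reword the phrase on linear regression prediction so that it says residual draws are added to the predictions.

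The cost is a few lines of text, a little computing time, and intervals slightly wider than ML imputation with ordinary pooling would give. Recruitment, assessments and the ANCOVA itself are unaffected.

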### Data monitoring

The independent data monitoring and safety committee is composed by experts in counselling and CBT interventions, gerontology, caregiver issues, elder abuse and personal rights. All members (see acknowledgement) are independent from the funder and competing interests. They will also be convened to detect any trends, such as increases in un/expected events, and take appropriate action, to seek additional advice or information from investigators where required, to evaluate the risk of the trial continuing and take appropriate action where necessary. The whole committee is planned to meet once a year. Specific experts can be contacted as needed.

### Harms

Adverse events of the intervention or assessment procedures are not expected. However, any adverse events or misconducts of interventionists are monitored throughout the trial. All data are logged and any serious adverse events are reported to the independent data monitoring and safety committee. In this case the committee will discuss any systematic adverse effects, suggest modifications in the protocol or the termination of the trial.

### Auditing

An independent data manager of the Centre for Clinical Studies of the Jena University Hospital will monitor the current study according the Quality Management and Monitoring Plan (e.g. checking completeness and correctness of study documents, study data, and data input) every 4–5 months.

### Protocol amendments

Because dropout rates have been lower than expected in this ongoing study, the aimed recruitment number has been reduced from 572 to 504 to achieve the planned study completer sample of 238 caregivers. In line with the changing actual national and local COVID-19 restrictions and official instructions of the participating long-term care insurances (restricted home visits), the following alternative settings for the initial home visit in *setting a* of intervention 1 are allowed: face-to-face contact in the service centre of the long-term care insurance or telephone-based initial contact. These possible setting variations because of actual restrictions will be considered in the data analyses.

## Discussion

This study aims to evaluate the effectiveness of a stepped counselling approach for burdened caregivers delivered by care counsellors of two long-term care insurances and registered psychotherapists. This stepped intervention approach can be tailored to specific caregiver’s risk and need profile (e.g. practical needs, emotions) in a resource efficient way. In contrast to most previous interventions that have been evaluated for specific caregiver subgroups (e.g. dementia-caregivers, stroke-caregivers, etc.) we include distressed caregivers of older adults with any chronic condition. With this broader target group, we assume to facilitate the uptake of the intervention in settings providing counselling services for all types of caregivers. The possibility to deliver the whole intervention by phone expands the access for caregivers in rural areas and facilitates future services in minority languages.

Furthermore, the ReDiCare study is one of the very few translational studies in caregiver intervention research and allows to evaluate the effectiveness of the intervention in real-world practice settings. With the randomized controlled design and the 6-month follow-up we also address methodological limitations of most previous translational studies in this field [11].

There are also limitations in this study. Because of the required informing of the participants in this pragmatic trial the participants are aware in which group they are allocated. Improvements of the intervention group can be biased from factors like motivation and expectations regarding the intervention (placebo), social contact with the interventionist, etc. Interventionists are also be aware that their interventions are evaluated and compared with other conditions. As in other psychosocial trials, the blinding of assessors is also questionable. When checking the caregiver assessments for unclear points and missing responses, participants can reveal information on the interventions that will allow the assessor to identify the treatment condition. While we include more types of caregivers than most other caregiver intervention studies, caregivers of adults aged less than 60 years are excluded due to the call for this proposal.

Despite these limitations, delivering the intervention within routine care settings will provide valuable insights not only on effectiveness but also on costs and crucial factors for training, maintaining, and implementing the two interventions. Therefore, we hope that the results of the ReDiCare trial will contribute to stimulate further implementation efforts in this field. The findings of the current study will be published in peer-reviewed journals and presented at scientific conferences. Besides the scientific dissemination, we want to present and discuss the results with decision makers, insurances, NGOs and caregivers’ representatives in a public final meeting and other settings.

## Data Availability

Materials and major components of the two interventions are published in German [26, 35]. Further information is available from KP and GW on reasonable request. This study protocol does not contain any data or results of the evaluation. Scientific trial members of the University of Jena, the Robert-Bosch-Hospital, the University of Hohenheim (health economic data), and the study statistician from the University of Ulm will have access to the final data set. To ensure confidentiality, data distributed to members of the study team will be blinded of any identifying participant information.

## Abbreviations

ADL: Activities of daily living
ANCOVA: Analysis of covariance
AOK: Local Health Insurance Fund
BerTA: Beratung und telefonische Therapie für pflegende Angehörige [counselling and telephone-based therapy for caregivers]
BI: Barthel Index
CBT: Cognitive behavioural therapy
CES-D: Center for Epidemiologic Studies Depression Scale
CSQ-8: Client Satisfaction Questionnaire
EBI: Extended Barthel Index
GAS: Goal Attainment Scaling
GBB-24: Giessen Subjective Complaints List
ICER: Incremental cost-effectiveness ratio
ITT analysis: Intention-to-treat analysis
LTC insurances: Long-term care insurances
MLMI: Maximum Likelihood Multiple Imputation
PAC: Positive Aspects of Caregiving
PATHEV: Patient Questionnaire on Therapy Expectation and Evaluation
PLiP: ProblemLösen in der Pflegeberatung [problem-solving in care counselling]
PRUQ: Psychosocial Resource Utilization Questionnaire for Family Caregivers of People with Dementia
RCT: Randomized controlled trial
ReDiCare: Relieving Distressed Caregivers
SACiP: Scale for the Multiperspective Assessment of General Change Mechanisms in Psychotherapy
SCQ-AV: Sense of Competence Questionnaire – Abbreviated Version
SGB: Social act
SPSI-R:S: Social Problem Solving Inventory – Revised: Short
State 1: Bavaria
State 2: Baden-Württemberg
Tele.TAnDem: Cognitive-behavioural therapy telephone-based intervention for family caregivers of people with dementia
TIDieR: Template for Intervention Description and Replication Checklist and Guide
-t_1_: Baseline assessment
t_0_: Allocation after -t_1_
t_1_: Assessment 3 months after t_0_
t_2_: Assessment 6 months after t_1_ (post-intervention)
t_3_: Assessment 6 months after t_2_ (follow-up)
VAS: Visual Analogue Scale
VR-12: Veterans Rand 12-item Health Survey
